## Abstract

**Background:**

Psychosis is a serious mental illness that typically emerges during early adulthood. The disorder is characterized by inactivity, cognitive deficits and the need for ongoing support. Regular exercise has mood enhancing and anxiolytic effects that could benefit this patient group. To date, few studies have examined the effects of prescribed exercise on autonomy, health and cognitive functioning in psychosis.

**Methods/Design:**

This is a single-center, randomized controlled trial (RCT) with a 3-month follow-up. Usual care plus a 12-week supervised exercise program will be compared to usual outpatient care alone. The primary outcome will be patient autonomy measured by the Camberwell Assessment of Need (CAN) schedule – clinician rated. Secondary outcomes include cardiovascular risk factors, cognitive functioning, substance abuse, body awareness, depression and mood state. Changes in inflammatory markers and microbiotica will be explored. The feasibility of using patients as exercise trainers will also be assessed.

**Discussion:**

The treatment potential for exercise in psychosis is large because most individuals with the disorder are young and inactive. The study is one of the first to comprehensively assess the effects of regular exercise in young adults with psychosis. Sessions will be closely supervised and adjusted to meet patient needs. Both the feasibility and treatment effects of exercise interventions in psychosis will be discussed.

**Trial registration:**

German Clinical Trials Register DRKS00008991 7 August 2015.

## Background

Psychosis is a serious mental disorder characterized by a loss of contact with reality and deterioration in social and occupational functioning. The most serious form of the disorder, schizophrenia, has a lifetime prevalence of 5.5 (SD = 4.5) in 1,000 persons [1]. The mean age of onset is 18 years in males and 25 in females [2]. Schizophrenia is associated with elevated suicide rates and an increased risk of premature death related to a range of comorbid somatic conditions [3]. Rates of depression vary between 25–81 % [4], and substance abuse is highly prevalent. Cognitive impairment is a core feature of schizophrenia, which can adversely affect occupational functioning and life quality [5]. Deficits typically appear in attention, declarative memory and higher-order problem solving [6]. The speed of processing, working and long-term memory can also be affected, as are abilities that are essential to school and working life. Several studies have proposed that neuroinflammation and autoimmunity are involved in the etiology and pathogenesis of schizophrenia [7, 8]. The stress-vulnerability model suggests that lowering biological vulnerability and reducing stress may help prevent relapse. Reducing biological vulnerability with medication remains a cornerstone of treatment. Increasingly, psychosocial interventions have also focusing on resilience to stress [9].

Inactivity is another key feature of psychosis; most individuals with the disorder do not meet the minimum physical activity levels recommended for general health [10]. This is problematic because regular exercise has positive neurobiological effects, which are likely to benefit this patient group. For example, exercise affects the hypothalamic-pituitary-adrenal (HPA) axis, which in turn modulates stress-reactivity [11, 12]. Exercise also influences hippocampal cell proliferation [13], and serotonergic release [14], producing an anti-depressant effect when performed regularly. Regular physical activity has been shown to lower systemic inflammation [15], which may be of importance in psychotic patients. According to three Cochrane reviews, physical exercise has moderate effects on depression equivalent to anti-depressant treatment [16–18]. Other beneficial effects include improved sleep quality [19] and increased neural growth factor expression, which affects neurogenesis, learning and memory [20]. Recent studies suggest that exercise may also reduce cravings for alcohol and other drugs in substance dependent individuals [21, 22]. Despite this evidence, few studies have explored the effects of exercise in patients with psychosis, a physically inactive patient group with high rates of comorbid depression and substance abuse.

The primary objective of FitForLife is to examine the effects of a 12-week physical exercise program on autonomy in young adults with psychosis. Secondary aims are to explore changes in general health, cognitive ability, substance use, body awareness, depression and mood states. Blood and feces samples will be requested to assess changes in inflammatory markers and microbiotica. The feasibility of educating patients as exercise trainers will also be assessed. We hypothesize that the intervention will lead to improvements in all outcomes assessed.

## Specific research questions

Specific research questions are as follows:Can a supervised exercise intervention for psychosis improve patient autonomy (that is, their need for care and assistance)?What are the effects of regular exercise on cardiovascular risk factors (body weight, waist and hip circumference, blood pressure, blood lipids), maximal oxygen uptake (VO_2 max_), and inflammatory markers?Can regular exercise improve cognitive functioning and body awareness in psychosis?Is regular exercise associated with reduced comorbidity, specifically, depression, anxiety and substance abuse?What are the effects of regular exercise on symptom recurrence and hospitalization?Does regular exercise improve the microbiotic profile of patients, and are these changes correlated with other health-related outcomes?What are the short-term (acute) effects of exercise on self-rated mood in psychosis?Is it feasible to train psychotic patients as exercise trainers and role models?

## Method/Design

### Setting

All patients will be recruited via the ‘Midhagen’ outpatient unit for young adults (aged 18 to 45 years) with first-episode psychosis. Located in central Stockholm, the clinic delivers need-based care with the aim of maximizing patient autonomy and life quality. Various interventions are offered, including counselling-support, medication and education. Clinical staff are specialized in psychiatry, clinical psychology or psychiatric nursing. Approximately 200 patients are registered at the clinic each year, and the majority has schizophrenia. A minority have schizoaffective disorder or drug-induced psychosis. If the number of patients willing to participate is insufficient, the study will extend to a second psychiatric outpatient clinic located about 20 kilometers outside Stockholm.

### Study design, randomization and blinding

Single-center, two-group parallel, randomized controlled trial (RCT) with a 3-month post-treatment assessment (study end-point). Random allocation of the patients will be performed externally. A psychiatric nurse and research-assistant will be trained to conduct patient assessments before and after treatment. Assessors will, in most instances, be aware of the patient’s treatment allocation. Genuine blinding of assessors is not feasible given the high degree of research assistant involvement in the project as a whole. It is also likely that many patients will discuss their treatment will the assessors. Patients randomized to the exercise intervention will also receive usual care for psychosis administered by their clinician. The comparison group in this study will be an active (wait-list) control group that will receive need-based care at the clinic only. This will normally consist of medication and counseling/supportive therapy as required. Changes on key outcomes will be compared before and after treatment within and between the two allocated groups. All patients in the control condition will subsequently be offered the exercise intervention after the first group have completed treatment; that is, 12 weeks after the baseline assessment. This second round of exercise sessions will be led by patients with psychosis who have been educated as trainers (see description below). The feasibility of using patients as trainers will be assessed through a qualitative survey conducted at the end of the study and reported separately. The flow of participants through the trial is shown in Fig. 1.

**Fig. 1 Fig1:**
[figure not shown]
CONSORT diagram showing the proposed flow of participants through FitForLife. FitForLife is a randomized controlled trial (RCT) comparing the effects of standard outpatient treatment for psychosis to standard care plus a 12-week supported exercise intervention. The trial includes an embedded study of the acute effects of exercise on mood states

### Affective responses to exercise

To assess the affective response of patients to acute (short-term) bouts of exercise, a separate study will be embedded within the RCT design. Patients will complete the Positive and Negative Affect Scale (PANAS) [23] 5 to 10 minutes before and after each exercise session. Changes in mood states over time will be examined and reported. Affective responses to acute bouts of exercise have been shown to predict rates of exercise adherence, and are therefore relevant to measure. Specifically, positive mood responses during and following exercise are associated with higher rates of future exercise adherence, whereas negative affective responses have been linked to lower rates of adherence [24].

### Ethics

The study has received ethical approval by the Regional Ethics Committee (Regionala Etikprovninsnämnden, EPN), Stockholm, number 2015/808-31/2. The trial is registered with German Clinical Trials Register: DRKS00008991. Informed consent will be obtained from all participants prior to inclusion. All patients must agree to participate voluntarily and will be free to withdraw from the study at any time. Patients randomized to usual care who express interest in receiving the exercise intervention will be given the opportunity to participate in the exercise treatment after the first wave of treatment is completed.

### Participants

The study will include 80 patients: 40 will receive the exercise intervention, and 40 will serve as active (wait-list) controls. Both new and existing patients will be invited to participate.

Inclusion criteria: All patients attending the clinic with a diagnosed first-episode psychotic disorder who provide informed consent and wish to participate will be included.

Exclusion criteria: Patients with severe somatic disorders or injuries that make it difficult or unsafe to exercise will be excluded. Patients with a history of cardiovascular disease and pregnant women will also be excluded.

### Screening interview

A research assistant or nurse will initially perform a brief screening interview at the clinic to determine patient eligibility using the criteria outlines above. Suitable patients will then be invited to participate in the trial, informed consent obtained, and a baseline assessment conducted prior to randomization.

### Baseline and post-treatment assessments

Assessments will include the following domains/measures:Demographics will be assessed, including age, gender, occupation, sick leave (baseline only; taken from patient files).Diagnosis, age of symptom onset, number of psychosis-related hospital admissions, medication use (also from patient files, where available) will be assessed.Autonomy will be assessed by the Camberwell Assessment of Need (CAN) – clinician rated questionnaire [25]. CAN is a validated instrument used to understand the health and social needs of adults with severe mental health problems. It covers 22 domains of an individual’s life, such as accommodation, self-care, daytime activities, psychological distress, physical health and relationships.Depression severity will be measured using the Montgomery-Åsberg Depression Rating Scale (MADRS) [26].Habitual physical activity levels ‘in a typical week’ (frequency and intensity) will be assessed using a questionnaire developed by the Swedish Institute of Sport and Health Science (GIH:Gymnastik- och idrottshögskolan) and previously used in a nationwide lifestyle study [27].Fitness will be assessed using a modified Åstrand VO2-submax cycle ergometer test [28].Height and weight will be assessed to estimate body mass index (BMI), waist and hip circumference and blood pressure.Body Awareness will be assessed by the Body Awareness Scale [29].Cognitive ability will be assessed by the CogState Brief Battery [30], Trailmaking [31] and Stroop tests [32].Blood and stool samples will be taken to test fatty acids, inflammatory markers (for example, IL-10, IL-1ra and TNF-alpha) and microbiotic profile (samples to be assessed within the Institute for Molecular Medicine and Surgery, Karolinska Institutet).

### Exercise intervention

Exercise sessions will be designed and supervised by exercise science graduates from the Swedish School of Health and Sports Medicine (GIH), under the supervision of an experienced exercise physiologist. GIH has extensive experience developing training protocols for patients with various health conditions. The graduates will also educate and support the six patients who volunteer to work as exercise trainers during the second phase of the study. Exercise sessions will be available five times/week during the 12-week intervention, and participants will be encouraged to attend three sessions each week. The training sessions will consist of a 5 to 10 minute warm-up, 30 minutes of aerobic training, 15 minutes of body-weight resistance training, and a 5 to 10 minute cool-down (about 1 hour in total). Participants will be encouraged to train at a level appropriate to their current fitness and ability, with the aim of reaching a moderate intensity (that is, three times or more higher that resting metabolic rate). Intensity and total training volume will be estimated from the accelerometer data and used in the analyses. To maximize participation and adherence, we aim to offer exercise classes that appeal to the participants, with varying types of exercises and shifting between indoor and outdoor activities. However, most sessions will be conducted indoors; outdoor sessions are dependent on weather conditions. Regular meetings will be scheduled with the trainers and participants to discuss the classes, and there will be capacity to adjust the activities. Six patient (three males, three females) will be invited to become exercise trainers for the second round of patients. Exercise science students from GIH will train these patients. The selection of patient-trainers will be made with clinical staff; six patients will be paid to lead regular exercise classes. The intention is that the trainers will serve as role models to increase participant empowerment.

### Objective assessment of physical activity

All patients randomized to the exercise group will be provided a hip-worn accelerometer (‘FitBit Zip’ device) to objectively measure and record daily physical activity levels, including the total number of steps taken and minutes/hours spent in light, moderate and vigorous activity. The device enables patients to set activity goals and receive daily feedback. It can be used with Smartphones and computers, and it is possible to store data from multiple devices centrally. This will be achieved using the online ‘Fitabase’ program.

### Statistical analysis

Participant characteristics, stratified by treatment group (exercise versus active control) will be presented. Baseline differences will be tested using t-tests for continuous variables and Chi-square tests for categorical outcomes. Parametric test assumptions will be examined and reported. Nonparametric data will be transformed or alternatively analyzed using nonparametric statistical tests. Multiple imputation will be used to replace missing internal values where appropriate. Within-group changes in the primary outcome (autonomy) and secondary outcomes (health, cognitive ability, substance use, etcetera) will be analyzed using paired sample t-tests. To address the primary research question, intention-to-treat analyses will be performed. The effect of group allocation on autonomy and all secondary outcomes at 3 month follow-up will be assessed using linear regression models (logistic for binary outcomes), using both the mean difference (baseline to 3 months) and total scores as dependent variables. Where the total score is used as the outcome, baseline group differences in covariates will be adjusted. Data from individual accelerometers will be pooled to objectively assess changes in physical activity levels before and after treatment. All analyses will be performed using SPSS 22.0. All tests will be two-sided and *P*-values of less than 0.05 will be considered statistically significant.

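### The primary CAN comparison may be made on the raw scale, on a transformed scale or by a nonparametric test, chosen after the data are examined and without a criterion; one baseline-adjusted model should be fixed instead

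*Protocol article*

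**What the plan says.** All of this is in the protocol article; no separate analysis plan is at hand.

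- The Abstract (Methods/Design) names the endpoint: "The primary outcome will be patient autonomy measured by the Camberwell Assessment of Need (CAN) schedule", clinician rated.
- Statistical analysis says "Parametric test assumptions will be examined and reported", and next "Nonparametric data will be transformed or alternatively analyzed using nonparametric statistical tests". It states no threshold, no order of preference between the two routes, and no named transformation or test.
- The between-group analysis comes later in the same paragraph: "The effect of group allocation on autonomy and all secondary outcomes at 3 month follow-up will be assessed using linear regression models", "using both the mean difference (baseline to 3 months) and total scores as dependent variables". Neither dependent variable is named as the primary one.
- Adjustment is limited: "Where the total score is used as the outcome, baseline group differences in covariates will be adjusted". Baseline CAN is not named as a covariate.
- Tests are two-sided, and P-"values of less than 0.05 will be considered statistically significant".
- On masking, Study design, randomization and blinding says "Genuine blinding of assessors is not feasible". The analyst is not mentioned.

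**The concern.** The text states a two-stage rule: look at the data, then choose among three kinds of analysis. Nothing takes CAN out of its reach. The three do not answer the same question. Raw-scale regression estimates a difference in mean needs. Regression on a log scale estimates something close to a ratio. A Mann-Whitney test addresses how often a patient in one arm scores above a patient in the other.

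Two things are at stake. If the choice is open, the nominal 5% no longer describes the error rate of the reported result. And if a two-group rank test on follow-up scores is used, baseline CAN, which is collected before randomization, cannot enter as a covariate.

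The switch is not needed to keep the test valid. With about 40 per arm, a linear model does not require normally distributed scores.

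**Working it through.** **Inputs from the document.** 80 patients, 40 per arm (Participants); two-sided 0.05 (Statistical analysis); CAN covers 22 domains (Baseline and post-treatment assessments). The article gives no effect size, SD or power, so there is no figure of its own to reproduce.

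**Assumptions, not in the document.** Effect 0 or 0.5 SD on a latent normal scale; latent baseline to follow-up correlation r = 0.3, 0.5 or 0.7; no dropout; a right-skewed CAN score from 0 to 22, generated as round(exp(1.4 + 0.6z)) and capped at 22. There were 6,000 simulated trials per setting. The Monte Carlo standard error at 0.05 is √(0.05 × 0.95 / 6000) ≈ 0.003.

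**Models.** Adjusted: follow-up = a + b·arm + c·baseline + error. Log-adjusted: the same on log(score + 1). Mechanical switch: Mann-Whitney on follow-up if a Shapiro-Wilk test on the adjusted model's residuals gives P < 0.05, otherwise the adjusted model.

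**Results, skewed scores.**

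| Analysis | Type I error, r = 0.3 / 0.5 / 0.7 | Power at 0.5 SD, r = 0.3 / 0.5 / 0.7 |
|---|---|---|
| Adjusted regression | 0.054 / 0.046 / 0.048 | 0.544 / 0.616 / 0.769 |
| Log-adjusted regression | 0.054 / 0.047 / 0.051 | 0.608 / 0.689 / 0.844 |
| Mann-Whitney, follow-up | 0.053 / 0.044 / 0.046 | 0.568 / 0.560 / 0.562 |
| Total score, unadjusted | 0.056 / 0.041 / 0.046 | 0.524 / 0.524 / 0.528 |
| Change score, unadjusted | 0.051 / 0.051 / 0.047 | 0.342 / 0.442 / 0.620 |
| Mann-Whitney, change | 0.048 / 0.054 / 0.046 | 0.360 / 0.470 / 0.675 |
| Mechanical switch | 0.053 / 0.045 / 0.046 | 0.569 / 0.565 / 0.584 |
| Smallest P of adjusted, log-adjusted, Mann-Whitney on follow-up | 0.080 / 0.081 / 0.095 | – |
| The same, plus both change-score analyses | 0.115 / 0.117 / 0.120 | – |

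**Reading the table.**

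1. *Validity.* The adjusted model stays near 5% throughout, and so does the mechanical switch. Inflation appears only when the smallest P-value is picked.
2. *Rank test on follow-up against the adjusted model.* The power difference is 0.544 − 0.568 = −0.02 at r = 0.3, 0.616 − 0.560 = 0.06 at 0.5 and 0.769 − 0.562 = 0.21 at 0.7. A separate run with negative-binomial scores (mean about 5, capped at 22; 3,000 trials) gave 0.67 − 0.57 = 0.10 at 0.5 and 0.82 − 0.58 = 0.24 at 0.7.
3. *The analyses the article names, unadjusted, against their own rank counterparts.* Total score 0.52-0.53 against 0.56-0.57; change score 0.34 / 0.44 / 0.62 against 0.36 / 0.47 / 0.68. Nothing is lost on switching.
4. *Adjusting only on an observed imbalance.* If baseline CAN enters only when a baseline t-test gives P < 0.05, power is 0.523 / 0.525 / 0.542, about the same as with no adjustment.

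**Check by formula, normal scores.** The standardized effect is 0.5 / √(2/40) = 2.236. Baseline adjustment divides it by √(1 − r²), giving 2.344, 2.582 and 3.131. Then Φ(value − 1.96) = 0.65, 0.73 and 0.88, against 0.61 unadjusted. The simulation with normal scores gave 0.63 / 0.72 / 0.86.

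**The case against.** **Scope.** The sentence follows the baseline t-tests and precedes the paired t-tests, so it may be meant mainly for those. That reading is possible, but the text does not limit the rule, and the regression sentence that follows does not exempt CAN.

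**Detail left to an analysis plan.** A missing trigger or test name alone would be no finding. Here the article states a rule, and a plan that fixed one primary model would have to override it.

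**Larger error rate.** A reader might infer a false-positive rate of about 11-12% from this sentence. That figure also needs free choice between change and total score, which comes from a different sentence, and deliberate selection by P-value. Picking only between a named unadjusted regression and its rank counterpart gave 0.062-0.072 in a further run (4,000 trials, negative-binomial scores).

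**Analyst unblinded.** A reader might also infer that the choice is made on unblinded data. The document says this only of assessors. It neither states nor rules out a masked check of pooled residuals.

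**Switching can help.** This stands. The first route listed is transformation, which keeps covariates and has more power than the raw scale when scores are skewed. At r = 0.3 the rank test also does slightly better than raw adjusted regression. It would be wrong to say that the rule has no benefit; what it does not do is protect type I error.

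**No adjustment to lose.** This stands in large part. The article never clearly commits to adjusting for baseline CAN, and a rank test on change would still use baseline by subtraction. The power gap is therefore measured against the model recommended here, not against one the article fixes.

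**Conclusion.** The point holds as one about an open, data-dependent choice for the primary outcome, and it should be changed. Its size is moderate. Under the assumed skewed scores, worst-case picking among adjusted, log-adjusted and rank analyses gives about 8-10% type I error. With a mechanical rule there is no inflation. Relative to a model adjusted for baseline CAN, a rank test on follow-up costs essentially nothing at r = 0.3, 5-10 points of power at 0.5 and about 20 at 0.7.

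These sizes rest on an assumed score distribution, an assumed effect of 0.5 SD, assumed correlations and no dropout, none of which the article gives. The documents do not show that the analyst is unblinded, or that the planned analyses would themselves lose power on switching. The benefit comes from committing to the baseline-adjusted model.

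**What to change.** For between-group comparisons, replace the transform-or-nonparametric sentence with one primary analysis that applies whatever the distribution: a linear model of end-point CAN on arm and baseline CAN, for all patients and regardless of any observed baseline difference, with HC3 robust or bootstrap confidence intervals. Label log-scale and rank-based (rank-ANCOVA) results as sensitivity analyses. This also settles the choice between change and total score for CAN, because with baseline CAN in the model both give the same arm coefficient.

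The cost is analysis wording only; baseline CAN is already collected. In power, HC3 intervals cost 1-2 points (0.67 to 0.66 at r = 0.5 and 0.82 to 0.80 at r = 0.7 in the negative-binomial run). If scores are strongly skewed, the raw-scale model gives up more against a log-scale one: 0.064, 0.073 and 0.075 from the table, and 0.03 at each correlation in the 4,000-trial run (0.62 / 0.69 / 0.83 against 0.59 / 0.66 / 0.80), so about 3 to 7.5 points.

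### Two co-equal regressions (change score and total score) are planned for the single primary outcome, with no rule for which one decides and baseline CAN a fixed covariate in neither

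*Protocol article*

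**What the plan says.** The abstract names one primary outcome: "The primary outcome will be patient autonomy measured by the Camberwell Assessment of Need (CAN) schedule – clinician rated". In the Statistical analysis section, the between-group comparison is a regression on allocation, linear for CAN and shared with the secondary outcomes. Two forms of each outcome serve as the response: "using both the mean difference (baseline to 3 months) and total scores as dependent variables". The section announces intention-to-treat analyses for the primary question but does not say which dependent variable they use.

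The rule on adjustment reads: "Where the total score is used as the outcome, baseline group differences in covariates will be adjusted". The same paragraph plans t-tests and Chi-square tests of baseline differences. No adjustment is given for the change-score model.

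One significance rule covers every test: "values of less than 0.05 will be considered statistically significant" is the wording applied to P, and the tests are two-sided.

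The Participants section fixes the size: "The study will include 80 patients: 40 will receive the exercise intervention, and 40 will serve as active (wait-list) controls". The sections on the screening interview and on assessments show that CAN is measured before randomisation.

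**The concern.** One outcome at one time point is given two between-group tests of equal standing, each at the full 0.05. The article does not say that one is primary and the other a sensitivity analysis, or that both must be significant. If the two results differ, the plan does not determine the trial's conclusion, and the choice could be made after the results are known. If either result may be claimed, the error rate for the primary question is above the stated 5%.

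The adjustment rule adds a second open choice. Covariates enter the total-score model because of baseline group differences, next to planned tests of those differences. The natural reading is that the covariate set depends on the observed data. Baseline CAN, usually the strongest candidate predictor of follow-up CAN, is therefore not guaranteed a place in either model.

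**Working it through.** **Inputs from the article.** 40 per arm; two-sided 0.05 for every test; two dependent variables; adjustment in the total-score model only.

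**Assumptions (not in the article).** Equal SDs at baseline (X) and 3 months (Y), scaled to 1; pre-post correlation ρ of 0.3, 0.5 and 0.7; normal data; no dropout; a true effect of 0.5 SD for the power figures.

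**Step 1. The plan's own figure: 5% per test.** In simulation with no effect (40 per arm, 20,000 trials per ρ), the change score gives 5.1%, 4.9% and 5.2%. The unadjusted total gives 5.0% throughout, and the total always adjusted for baseline CAN gives 5.1%, 5.1% and 5.2%. The total adjusted only when baseline CAN differs at p<0.05 gives 4.8%, 4.4% and 3.6%. No model taken alone is anti-conservative.

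**Step 2. Correlation of the two tests.**
- Change with unadjusted total: cov(Y−X, Y) = 1−ρ and var(Y−X) = 2(1−ρ), so the correlation is √((1−ρ)/2) = 0.59, 0.50, 0.39.
- Change with adjusted total: cov(Y−X, Y−ρX) = 1−ρ² and var(Y−ρX) = 1−ρ², so the correlation is √((1+ρ)/2) = 0.81, 0.87, 0.92.

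**Step 3. Chance of at least one false positive.** This is the bivariate-normal probability that either statistic exceeds 1.96 in absolute value, or simulation for the selective rule.

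| Total-score model | ρ = 0.3 | ρ = 0.5 | ρ = 0.7 |
|---|---|---|---|
| Always adjusted for baseline CAN | 7.8% | 7.3% | 6.8% |
| Adjusted only if baseline CAN differs at p<0.05 (simulated) | 8.5% | 8.3–8.6% | 7.9–8.0% |
| Not adjusted | 8.8% | 9.1% | 9.4% |

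Simulation of the always-adjusted case gives about 6.7–7.7%, which agrees with the formula to within simulation error. Two independent tests would give 1 − 0.95² = 9.75%, so the correlation keeps every figure below that.

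**Step 4. If both had to be significant.** P(both) = 5% + 5% − P(either). Unadjusted: 10 − 8.8 = 1.2% to 10 − 9.4 = 0.6%. Always adjusted: 10 − 7.7 = 2.3% to 10 − 6.7 = 3.3%. Under selective adjustment the total-score error is itself at most 5%, so the joint error is lower still. All are below 5%.

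**Step 5. Disagreement.** At a true 0.5 SD and ρ = 0.5, one model is significant and the other is not in about 18% of simulated trials if baseline CAN is always in the total-score model. The share is about 30–33% if it is adjusted selectively or not at all.

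**Step 6. Precision (secondary).** The variance factors are 2(1−ρ) for change, 1 for the unadjusted total and 1−ρ² with baseline CAN always included. At ρ = 0.5 these are 1.00, 1.00 and 0.75. Power at 0.5 SD with 40 per arm:

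| Model | ρ = 0.3 | ρ = 0.5 | ρ = 0.7 |
|---|---|---|---|
| Change score | 47% | 60% | 81% |
| Total, unadjusted | 60% | 60% | 60% |
| Total, baseline CAN always included | 63% | 72% | 87% |

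**The case against.** **The article states no either-model rule.** This is correct. The inflation in Step 3 is conditional, and requiring both results would bring the error below 5%. A reader might infer that the false-positive rate simply rises to about 9%. The text does not support that, because it leaves the decision rule open and does mention adjustment of the total-score model. The 8.8–9.4% range belongs only to the reading in which baseline CAN is never adjusted.

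**The precision argument is a matter of preference.** This is largely correct. In a randomised trial the change-score comparison is valid; it over-corrects only conditionally on a chance imbalance. A reader might infer that both stated models are less precise than a baseline-adjusted one. That is not established: if baseline CAN is always among the adjusted covariates, the total-score model already is that model. The loss also depends on a correlation the article does not give. At 0.7 the change score loses little (81% against 87%), and at 0.3 the unadjusted total loses little (60% against 63%).

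**A separate analysis plan may settle it.** It may, but the article is not silent here. It prescribes both regressions without priority, so a later plan naming one would have to depart from the published wording.

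What stands is that no model is decisive and no baseline covariate is fixed.

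**Conclusion.** The point holds as a badly fixed rule for the primary conclusion. Two regressions of CAN are each tested at 0.05, neither is decisive, and baseline CAN is fixed in neither. If either may be claimed, the error rate is between about 6.7% and 9.4%, depending on how the adjustment sentence is read. The two readings that respect that sentence give 6.7–7.7% and 7.9–8.6%. The inflation is moderate. The more practical problem is that at a moderate effect the two models would disagree on significance in roughly one trial in five to one in three (ρ = 0.5), with no rule for the conclusion.

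These sizes rest on assumed correlations, equal SDs, normal data and no dropout. The absence of a decision rule rests on the text alone. The gain in precision is a supporting reason for the fix and is not an error in itself.

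**What to change.** Name one decisive primary analysis: linear regression of the 3-month CAN total on allocation, with baseline CAN as a pre-specified covariate whatever the baseline tests show, in all randomised patients. Report the adjusted mean difference with its 95% CI and base the primary conclusion on it alone. Label the change-score regression as supportive, with no bearing on that conclusion. Drop the choice of covariates by observed baseline differences. Using the same model for continuous secondary outcomes is optional.

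The cost is a few sentences of analysis wording, with no new data, patients or procedures. The Trial status section places the article before the start of the trial, so at that point the change could precede any data. The single model keeps the error at 5% (simulated 5.1–5.2%). Its power is at least that of either stated model at every correlation examined.
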